## Methods and Analysis

### Study Design and Hypotheses

Participants are randomized to one of two conditions (1:1) testing four 30-min sessions delivered over 4 weeks. A blocked randomization procedure with random blocks sizes 10 and 20 was used to generate the randomization list. The *in vivo* group receives in session NRT sampling with a focus on expectancies for medication and experience using the medication in session. The counseling group receives standard smoking cessation behavioral counseling. All participants receive NRT for 13 weeks with additional nonintervention follow-ups at 1-, 3-, and 6-months post-intervention. Thus, all participants receive almost the same level of evidence-based medication (*in vivo* group receives an additional 2 weeks during sessions 1 and 2); the only differences are the process of introducing it (guided sampling vs. not) and the difference in behavioral sessions (e.g., focus on experience with medication vs. standard smoking cessation behavioral strategies). Specifically, the patch and lozenge were chosen, and the dosage and duration of use were based on standard of care practices (49, 50). These products were chosen because the patch provides a steady dose of nicotine throughout the day while the lozenge is a short-acting NRT, which can help curb cravings in the moment (51). Nicotine gum is another over-the-counter, short-acting option, however using gum requires dentation. Unlike the nicotine inhaler and nasal spray, the patch and lozenge do not require a prescription (44). All procedures are approved by the institutional review board at the University of Alabama at Birmingham (UAB). It is expected that individuals who experience the effects of the medication during sessions will have increased adherence and cessation relative to participants who receive standard smoking cessation counseling.

Importantly, sessions began in person for the first 364 participants, but were changed to primarily remote sessions as COVID-19 precautions were put in place, with 273 participants completing a combination of in-person sessions and some remote sessions. After 6/1/20, the study procedures were modified so that participants are now required to attend an in-person baseline visit with the remaining nine appointments conducted remotely. Participants complete the sessions (*in vivo* or standard counseling) over the phone with study staff and complete all study measures *via* email, text, or verbally over the phone.

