### Outcomes

The primary outcome variable will be smoking 7-day point prevalence abstinence confirmed by a CO ≤ 3ppm (if measured using the Vitalograph) or CO <6 ppm [if measured using the iCO Smokerlyzer; (55, 56)] at the 6-month follow-up. We will also examine abstinence across the study using the same CO-verified self-reported 7-day point prevalence abstinence. A secondary outcome includes medication adherence (defined as using >80% of doses) during the 10-week intervention period between groups. Adherence is assessed by self-report using timeline followback (TLFB) methods and prior to COVID, included verification through returned patches and blister packs of lozenges. Additional outcomes of interest include quitting across time and incidence, frequency, and duration of quit attempts. If participants are using other tobacco products, this will be reflected in the tobacco-use survey used to determine 7-day point prevalence abstinence for all products (e.g., e-cigarettes, cigars, chew/dip, etc.) as well as in the CO data for products that increase expired CO. In addition, this will be regarded as continued tobacco use and not as quit. Similarly, if participants are smoking other substances (e.g., cannabis) and are over the CO cutoff, regardless of self-report, they will be considered as smoking as we cannot separate the source of smoke through CO at follow-up. This is more conservative but given the high rates of comorbid tobacco and other drug use, particularly cannabis, it is unlikely they would stop one smoking behavior but continue the other.

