Exploratory moderation analyses will be conducted to determine whether baseline psychosocial variables such as ethnoracial identity, gender, educational attainment, and annual income, or smoking characteristics such as motivation to quit, abstinence self-efficacy, prior use of NRT, and abstinence-related expectancies moderate the relationship between intervention group and abstinence. These analyses will be conducted by fitting models with interaction terms for study group by moderator. We will also conduct mediation analyses (58, 59) to determine if factors such as medication adherence, withdrawal and craving, treatment engagement, and motivation to quit mediate the effect of intervention group on abstinence. These analyses will be conducted using path modeling to partition the intervention effect into direct and indirect. Lastly, we will examine treatment retention (% of people who were not lost to follow-up at 6-months), and engagement (# of study appointments completed) as well as therapist ratings for participants who completed study visits all in person, all remote, or a mixture of both modalities.

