### Remote Research Implications

#### General Methodology

While the present intervention was initially intended to be conducted as an in-person intervention across all study time points, recruitment and study procedures were adjusted to limit staff-participant contact given the development of the COVID-19 pandemic. Therefore, the intervention was modified to include one initial in-person baseline visit (primarily to verify smoking status and provide participants with the treatment manual, iCO monitor, and NRT products), with the remaining visits being conducted remotely. The circumstances of the pandemic led to the realization that some research procedures might benefit from the convenience and versatility of remote methods. For example, an increasing number of assessments are now being completed through platforms such as REDCap and Qualtrics, and it is plausible that entire interventions could be adapted to other remote modalities (i.e., phone calls, videoconferencing;53). In addition, consenting procedures as well as recruitment advertising can be easily performed remotely (63). Our team's adaptations for this study suggest that it is feasible to not only deliver smoking cessation interventions and counseling over the phone, but also to give smokers instructions on how to use NRT remotely, even in difficult to reach populations such as the CL population. If medication adherence and cessation outcomes are similar or better for those who complete study procedures remotely, these findings could provide support for moving to a more remote model of research. We plan to conduct a secondary data analysis to compare recruitment rate and retention between those who completed the study pre-pandemic to those post-pandemic.

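### Comparing retention and engagement between groups defined by the modality of visits completed builds a survivor bias into the comparison

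*Protocol article*

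**What the plan says.** The last planned analysis under Sample Size Considerations and Data Analysis examines "treatment retention (% of people who were not lost to follow-up at 6-months), and engagement (# of study appointments completed"), together with therapist ratings, "for participants who completed study visits all in person, all remote, or a mixture of both modalities". The groups are therefore described by the visits that people completed.

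Study Design and Hypotheses explains how the modalities arose. The first 364 participants began in person, 273 had a combination of in-person and remote sessions, and after 6/1/20 "participants are now required to attend an in-person baseline visit with the remaining nine appointments conducted remotely".

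General Methodology, in the Discussion, adds a second comparison: "We plan to conduct a secondary data analysis to compare recruitment rate and retention between those who completed the study pre-pandemic to those post-pandemic". Just before that it draws a conditional inference. "If medication adherence and cessation outcomes are similar or better for those who complete study procedures remotely", the findings could support a more remote model of research.

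Under Outcomes, abstinence is confirmed by "CO ≤ 3ppm (if measured using the Vitalograph) or CO <6 ppm" on the iCO Smokerlyzer. Adherence is more than 80% of doses by timeline followback (TLFB) self-report, which "prior to COVID, included verification through returned patches and blister packs of lozenges".

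**The concern.** The grouping variable and the outcome are both made of attendance. A person who enrolled before the switch can be labelled mixture only by still attending when visits became remote. A person on the same schedule who left earlier is labelled all in person. The mixture group is thus selected for staying, and the all-in-person group collects the dropouts whom the mixture group would otherwise have contained. The number of appointments completed is distorted in the same direction.

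The article intends to learn from these data whether remote delivery is workable in a population that is hard to retain. A retention advantage for participants with remote visits would be read as evidence for that, although the labelling alone can produce it.

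**Working it through.** The plan gives no figure for this comparison, so there is none to reproduce. The check is what the stated labelling yields when modality has no effect at all.

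**Inputs from the protocol article**
- Recruitment goal 517, of whom the first 364 began in person; 517 − 364 = 153 enrol later (Participants; Study Design and Hypotheses).
- Ten visits: baseline, sessions 1–4, weeks 8 and 12, months 1, 3 and 6 (Table 1).
- 25–30% missed appointments up to 6 months (Limitations and Strengths).

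**Assumptions**
- The midpoint, 27.5%, is permanent loss, so 72.5% are retained.
- Dropout is equally likely at each of the nine post-baseline visits, in every modality.
- Visits fall at weeks 0, 1, 2, 3, 4, 8, 12, 16, 24 and 36.
- The first 364 enrol evenly over 60, 104 or 160 weeks before the switch. The article does not give this span.

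**Step 1: by hand.** Per-visit staying probability is q = 0.725^(1/9) = 0.9649. Take participants whose switch falls between week 12 and month 1. To be labelled mixture they must attend month 1, the seventh post-baseline visit, with probability q^7 = 0.779. Their retention is then q^2 = 0.931. The other 22.1% left earlier, are labelled all in person, and have retention 0%. True retention is 0.779 × 0.931 = 0.725 for the whole cohort, yet the two labels show 93.1% and 0%.

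**Step 2: the whole trial, by simulation.** Apparent 6-month retention:

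| Enrolment span before switch | Baseline counts: all in person | Baseline counts: mixture | Baseline not counted: all in person | Baseline not counted: mixture | Baseline not counted: all remote |
|---|---|---|---|---|---|
| 60 weeks | 52.9% | 84.7% | 58.2% | 93.7% | 75.1% |
| 104 weeks | 63.6% | 82.3% | 68.2% | 93.8% | 75.1% |
| 160 weeks | 67.0% | 80.6% | 71.2% | 93.8% | 75.2% |

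- If baseline counts, mean visits completed are 7.3–8.2 all in person and 9.1–9.4 mixture, against a true mean of 8.56 for everyone.
- If baseline counts, nobody can be all remote on the schedule in force after 6/1/20, since that visit is in person.
- If baseline is not counted, all remote is populated. Its 75% is q^8 = 0.751, because only people who attended session 1 can be labelled. About 517 × (1 − 0.9649) = 18 people with no post-baseline visit fall into no group.

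**Step 3: a different dropout model.** With a constant dropout rate per week, 25% or 30% lost, and spans of 52, 104 or 156 weeks, the gap between mixture and all in person is about 16 to 36 points if baseline is not counted. If baseline counts, it is about 8 to 31 points. The direction never changes.

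**Step 4: relabelling.** Grouping the same simulated people by the modality scheduled at enrolment returns 72–73% in every group, which is the truth.

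**Step 5: the pre- and post-pandemic comparison.** It would "compare recruitment rate and retention between those who completed the study pre-pandemic to those post-pandemic". Taken literally, people who completed the study are all retained, so the comparison would be uninformative.

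**The case against.** Much can be said for the plan.

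- A reader might infer that retention is fixed by definition. The article does not support this. It defines retention by people not lost to follow-up, which presupposes that some were lost, so the natural reading is biased retention, not 100% in every group. The phrase about those who completed the study is probably loose Discussion wording, since recruitment rate makes no sense among completers.
- A reader might infer that the all-remote group is empty. This holds only if baseline counts. Table 1 sets baseline apart from the post-randomisation schedule, so the participants enrolled after 6/1/20 may well be the intended all-remote group. In that case the spurious gap between all remote and all in person is smaller: about 4 points at 160 weeks (75.2% against 71.2%) and 17 at 60 weeks (75.1% against 58.2%).
- The 273 mixed participants cannot be split with certainty. If all come from the first 364, 91 of those are not mixed; the text does not settle this. The simulated spans were not fitted to that count.
- A reader might infer that the adherence rule changed, or that the two CO cut-offs differ in strictness. Only the returned-product check stopped; the rule of more than 80% by TLFB stayed. Device-specific cut-offs do not by themselves show different stringency. The statement on adherence and cessation is also a conditional remark, not a specified analysis.
- Group definitions for an ancillary analysis are often left to a fuller document.

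All of this limits the point, but the core stands. The article itself states a grouping by visits completed and sets it against retention and visits completed. A fuller plan would have to replace that rule, not merely add detail to it.

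**Conclusion.** The point holds for the comparison by modality of completed visits. With no modality effect, the labelling makes mixture look better retained than all in person by roughly 14 to 32 points if baseline counts (80.6 − 67.0 = 13.6; 84.7 − 52.9 = 31.8). If baseline is not counted, the gap is 23 to 36 points (93.8 − 71.2 = 22.6; 93.7 − 58.2 = 35.5).

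The direction follows from the labelling. The size rests on the assumed enrolment span, on reading missed appointments as permanent loss, and on equal dropout per visit; the per-week dropout model gave gaps as small as 8 points.

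The adherence and cessation question is secondary and conditional. It matters only if those outcomes are compared between periods, because the CO device with its cut-off and the returned-product check changed along with the modality.

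A reader might also infer that the trial's main result is compromised. The documents do not support that. Allocation was 1:1 in blocks and both arms went through the same switch, so neither the randomised primary comparison nor the sample size is affected.

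**What to change.** - Define the groups by enrolment period and scheduled modality, fixed at randomisation: all visits due before the switch, schedule straddling the switch, and enrolled after 6/1/20. State whether baseline counts as a visit.
- Keep everyone randomised in the denominator for retention, and compare attendance per scheduled visit instead of a raw count of visits.
- Reword the pre- and post-pandemic comparison so that it covers all participants enrolled in each period, not those who completed the study.
- Label these contrasts as non-randomised, since period and modality changed together.
- If adherence or cessation is compared between periods to support a remote model, use TLFB self-report adherence in all periods, and add self-reported abstinence as a sensitivity analysis beside the CO-verified outcome.

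The cost is analysis wording only. Enrolment dates and visit schedules are enough to form the groups, and no new data are needed.

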## Discussion

### Significance

The present intervention evaluates whether *in vivo* sampling of NRT can lead to increased smoking abstinence rates compared to standard behavioral smoking cessation treatment among individuals in the CL system. As mentioned earlier, both groups receive NRT although only the *in vivo* group receives guided and structured sampling in real time with a counselor. If the proposed hypothesis is supported, this intervention could serve as a novel strategy that improves NRT adherence in a quit attempt among individuals in the CL population. The protocol outlined above is feasible to conduct in a wide variety of settings and requires minimal training from staff. In fact, non-therapist, bachelor's-level research assistants trained on both interventions following a therapist manual are the individuals responsible for administering the intervention, underscoring the translatability of this intervention in under-resourced settings. Specifically, the findings will especially benefit individuals involved in the CL system, a population for which smoking cessation interventions are lacking and tobacco use prevalence is high. The low cost and availability of NRT in the U.S., in addition to the limited resources necessary for the intervention, make it easily implementable in community programs as well. Furthermore, the intervention could also be implemented in other settings, such as homeless shelters and hospitals, as those are opportune locations to intervene with under-resourced populations with high smoking rates (60, 61). Initially, training members of the community in this intervention would be required but in the long run, given the impact of smoking on one's health and quality of life, the benefits outweigh the initial costs. While this intervention is specific to NRT, the protocol could potentially be adapted to other smoking cessation medications with low adherence [e.g., varenicline; (62)] as well as other health conditions (e.g., diabetes management) where medication adherence is low.

### Remote Research Implications

#### General Methodology

While the present intervention was initially intended to be conducted as an in-person intervention across all study time points, recruitment and study procedures were adjusted to limit staff-participant contact given the development of the COVID-19 pandemic. Therefore, the intervention was modified to include one initial in-person baseline visit (primarily to verify smoking status and provide participants with the treatment manual, iCO monitor, and NRT products), with the remaining visits being conducted remotely. The circumstances of the pandemic led to the realization that some research procedures might benefit from the convenience and versatility of remote methods. For example, an increasing number of assessments are now being completed through platforms such as REDCap and Qualtrics, and it is plausible that entire interventions could be adapted to other remote modalities (i.e., phone calls, videoconferencing;53). In addition, consenting procedures as well as recruitment advertising can be easily performed remotely (63). Our team's adaptations for this study suggest that it is feasible to not only deliver smoking cessation interventions and counseling over the phone, but also to give smokers instructions on how to use NRT remotely, even in difficult to reach populations such as the CL population. If medication adherence and cessation outcomes are similar or better for those who complete study procedures remotely, these findings could provide support for moving to a more remote model of research. We plan to conduct a secondary data analysis to compare recruitment rate and retention between those who completed the study pre-pandemic to those post-pandemic.

#### Remote CO Collection

When the study began, carbon monoxide (CO) readings were captured using a Vitalograph CO Monitor. In order to be eligible for participation, participants' CO reading must be >10 ppm at baseline, and if their CO reading is 3 ppm or less (as measured by the Vitalograph) at follow-up assessments, they are considered abstinent from cigarettes. The study protocol was modified as in-person recruitment resumed. Since the new procedures included only one in-person visit, adjustments were necessary so study staff could continue to monitor the participant's smoking status remotely. Study staff continue to use the Vitalograph at the in-person baseline visit as well as train participants to use a take-home device, the Covita iCO Smokerlyzer as mentioned earlier. Study staff assists the participants with downloading the app, setting up an account, and walking through the procedures to complete a breath sample using the participants' own phones at the baseline appointment. The recommended cutoff to determine abstinence with this device is <6 ppm (55, 56).

#### Therapeutic Interaction

The central premise of the presented *in vivo* exposure is to have a trained bachelor's level therapist present while the participants try the cessation medication and explore expectancies and their experiences with using NRT. As previously mentioned, the therapist encourages participants to provide feedback (both positive and negative) on the use/experience of the medication, helps address any possible side effects, and provides additional product information. It is possible that this therapeutic interaction may be affected by the modality of the interaction (64, 65) (i.e., in person vs. remote). While therapeutic alliance may be comparable in remote vs. in-person sessions, each modality has specific challenges. For example, in-person sessions bring with them the logistical challenges of traveling to an in-person appointment, while a barrier to remote sessions could be limited access to technology or low technology literacy.

### Limitations and Strengths

While the intervention described presents numerous benefits and provides novel contributions to the field, several limitations should be noted. One potential limitation is that the intervention is not particularly tailored to the needs of the CL population. While it cannot be overlooked that those in the CL system have many important needs (e.g., financial, housing, and employment assistance), smoking cessation interventions remain extremely important (3, 4) especially given the negative health effects of smoking. Though these structural barriers cannot be fixed with a single intervention, evidence suggests that medication adherence is a critical target for increasing abstinence (33, 34) and that experience with smoking pharmacotherapy may be an important way to improve medication adherence in this population (23). With limited access to healthcare resources for extended periods of time, implementing a smoking cessation treatment plan into CL operations gives individuals the otherwise difficult-to-access opportunity to get help quitting smoking, which will ultimately lead to better health outcomes. It can also be argued that another weakness of the study is that the treatment is not imbedded in the community corrections system. However, this is a limitation inherent in most research that tests the efficacy of a new approach prior to expanding into more implementation science research, in this case with the community corrections staff.

An additional limitation of the present intervention could be that it is not intensive enough to promote a change in smoking behavior. A sampling intervention such as this may not provide the intensive and prolonged treatment that is necessary for a chronic relapsing condition such as smoking (66). However, time and resource-heavy interventions are unlikely to be implemented in busy clinical or low-resource settings. The proposed intervention was designed to be brief and simple enough to be implemented in busy settings by non-therapist providers but still intensive and targeted to encourage behavior change. While the PI is not a Tobacco Treatment Specialist (TTS) and the staff were not sent for specific TTS training, they are a clinical psychologist with research and clinical experience in both treating and training other clinicians about tobacco treatment,. Furthermore, RA level staff completed the counseling treatment fidelity ratings rather than a clinical supervisor or an outside clinician. Finally, as previously mentioned, intervention procedures were adapted in order to reduce staff-participant contact as the COVID-19 pandemic evolved. While necessary, these adjustments (e.g., primarily conducting remote sessions) could negatively affect the *in vivo* experience and impact the therapeutic interaction. Additionally, another potential issue in the study is the ability to retain participants until study end. Oftentimes people in the CL population have unpredictable lives, where unstable housing situations, cell phone access, transportation, etc. can impact participants' ability to adhere to the study protocol (67). Missed appointments are expected to be similar to our previous study (25–30% missed appointments at any point up to 6 months post intervention). The analytical approach will use all available data adjusted for characteristics relevantly associated with attrition, if any, and thus decreasing potential bias from missing data (57).

Nevertheless, the integrity of the intervention is generally maintained through phone calls with participants, where they can share feedback and discuss questions with the study staff. Further, with the use of the iCO, biochemical verification of smoking status is maintained at all study visits, a significant strength. A final strength of this study was the comparison group (four 30-min behavioral smoking cessation counseling sessions); thus, if the *in vivo* intervention shows stronger cessation results over the current standard, this will provide an important advance in smoking cessation treatment.

